### Statistics

#### Sample size

The sample size estimate was calculated based on the primary outcome of scar thickness at 6 months post burn for one scar site. We assumed a pooled standard deviation of 1.0 mm based on a retrospective audit of data from our centre. To detect a statistically significant between-group difference of 0.76 mm in scar thickness with 80% power and an alpha value of 0.017 (due to three pairwise comparisons), 36 participants are required in each of the three groups. Assuming a 20% dropout, the total number of participants who need to be recruited at baseline is 135 (45 participants per group).

#### Data analysis

Sociodemographic, clinical and intervention data will be summarised using descriptive statistics. For continuous outcomes either mean and standard deviation, or median and range will be used depending on the distribution of the variable. For categorical outcomes frequency and percentage will be reported. Data related to intervention benefits will be analysed on the ‘intention-to-treat’ (ITT) principle, defined as participants analysed according to their randomly allocated study group regardless of treatment received who complete follow-up data collection and who receive the recommended length of intervention. Data related to intervention adverse effects will be analysed according to the ITT principle as well as per protocol defined as those who received and commenced the intervention. A sensitivity analysis will be conducted to compare the ITT and per-protocol approaches if appropriate. Baseline characteristics will be compared to assess the compatibility of groups. At baseline between-group differences will be investigated using linear regression for continuous data and Fisher’s exact test for categorical data. Post-baseline, between-group differences in adherence will also be investigated using linear regression at each time point. Potential confounding variables for the primary outcomes are considered a priori to be: age, days to re-epithelialisation, percentage maximum burn depth, days post burn when scar management commenced, Fitzpatrick skin type, percentage TBSA burned, patient adherence, level of pressure beneath garment (for the groups treated with pressure garments), anatomical body site treated, surgical intervention received (skin grafting in the acute phase, spontaneous wound healing in the acute phase, post-acute reconstructive surgery), wound complications (e.g. infection), other interventions received (e.g. massage) including the use of medications for itch [8, 9, 48].

The primary outcomes will be analysed using mixed effects regression analyses to examine differences at 6 months post burn, adjusting for the baseline value of the outcomes. Mixed effect regression analyses will be completed for each follow-up time point. Potential confounding variables that are identified as imbalanced between the groups will be entered into regression analyses. The time-varying covariates are patient adherence, level of pressure beneath garments, and other interventions received. All of the other potential confounding variables are non-time-dependent covariates. Sensitivity analyses will be completed for missing data using multiple imputation of missing observations by creating ten complete data sets [49] of missing dependent and independent data. For participants from whom data is collected from two scar sites, the multiple sites on these individuals will be accounted for in analytic models by including the scar site as a random effect nested within participant. Initially all participants will be included in the analyses. The analyses will then be repeated after stratifying by surgical intervention (i.e. skin grafting in the acute phase, spontaneous skin healing in the acute phase, post-acute reconstructive surgery). Subsequently, the influence of sociodemographic, clinical and intervention factors, and primary and secondary outcomes not included as dependent variables, on primary and secondary outcomes will also be examined using regression models. Differences in health-related quality of life between the intervention group and respective normative comparison groups will be analysed using *t* tests, z-scores, or equivalent nonparametric tests where appropriate. Differences in self-reported outcomes by children versus caregivers, between age groups and in comparison to normative data will also be examined using univariate statistics such as *t* tests, z-scores, or nonparametric equivalents. Significance will be set at less than 0.05. Data will be analysed using SPSS (SPSS Inc., Chicago, IL, USA) or Stata (StataCorp, College Station, TX, USA) where appropriate.

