Silicone products can include topical silicone gels, silicone gel sheets, silicone sprays and silicone oils [22]. A film-forming topical silicone gel was selected for inclusion in this study as topical silicone gels have been recently recommended over other silicone products in clinical practice guidelines as they are thought to result in fewer adverse effects [23]. Strataderm® topical silicone gel, a product used in the participating burns department prior to the trial commencing, has the advantage of a reduced frequency of application (once per day as opposed to twice per day) compared to other topical silicone gel products. It, therefore, has the potential to reduce the treatment burden to patients, improve adherence and reduce the cost of scar prevention and management compared to other scar therapies. Whilst the exact mechanism of action of topical silicone gels has not been confirmed [22–24], it is hypothesised that the occlusive nature of the gel reduces transepidermal water loss, thus increasing the hydration of the stratum corneum [25, 26]. This results in a ‘normalising’ of the cellular processes of the skin, consequently reducing collagen production [25, 26]. Topical silicone gel may also provide a protective barrier against environmental contaminants [25, 26]. It is important to note, however, that whilst there is a reduced risk of adverse effects with the use of topical silicone gels there is still a risk of local dermatological reactions [25].

Pressure garment therapy also works to normalise cellular processes; however, it does this through mechanical pressure. Pressures of 15 to 25 mmHg are hypothesised to reduce capillary flow [13, 18], thus limiting oxygen and nutrients in the affected area and preventing collagen production [27]. The burden of pressure garment therapy to patients and their families, however, can be high if recommended wearing times of 23 h per day for up to 18 months or until scar maturation are followed [2, 28]. Adverse effects from pressure garment therapy can include skin breakdown, altered bone growth and psychological distress from cosmetic differences [2, 5, 7, 29]. The burden of treatment and the presence of adverse effects can impact patient adherence to recommended prevention strategies and requires careful consideration when evaluating the effectiveness of these interventions.

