### Discontinuation/adverse events

The proposed interventions are considered to be part of standard care at the participating burns centre; therefore, minimal adverse events are expected. Known potential adverse events (e.g. a skin rash from topical silicone gel or skin damage from friction caused by pressure garments) have a standardised management protocol at the participating health service. Adverse effects of scar interventions will be monitored by reviewing patient medical records and by the self-report of caregivers, child participants (where appropriate) and treating therapists. All adverse effects will be reported to the clinical health service and the overseeing Human Research Ethics Committee. Discontinuation or alteration of treatment will be at the discretion of the treating clinical team and will be monitored throughout the study. At the conclusion of the study participants will receive standard care.

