## Discussion

Silicone products and pressure garment therapy have been accepted treatments for burn scar management in high-income countries for over 40 years, though there is minimal evidence to support their use [5, 7, 10, 13]. In addition, minimal research has been completed with a paediatric burns population or with any age group using a broad evaluation that investigates the effectiveness of scar prevention interventions, their impact on health-related quality of life, the burden of treatments on patients and their families, or the paediatric patient’s adherence to these interventions.

Whilst little is known about adherence to recommended wear and care regimes for children using topical silicone gel and/or pressure garments, adherence by children is likely less than optimal. In adults, adherence to recommended pressure garment therapy has recently been recorded as 15 to 80% with reasons for nonadherence including the cosmetic appearance of garments, insufficient education regarding garment use as well as poor fit and discomfort [50]. Low rates of adherence to recommended silicone gel sheeting use (24 h per day) have also been reported in adults [51]. It is expected that adherence will be greater when using topical silicone gel (Strataderm®) compared to pressure garment therapy due to its reduced application time and there being no need for additional care/maintenance of the product.

The burden of topical silicone gel also appears lower than pressure garment therapy due to recommended application of the product once or twice daily (depending on scar location), fast drying time and durability. However, topical silicone gels may be time-consuming to apply to an extensive body surface area and have been documented to cause local dermatological reactions [25]. Thus, further investigation of their effectiveness is required.

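### The analysis set labelled intention-to-treat is limited to children who finish follow-up and the recommended treatment length, so as written the primary comparison is made in a completer subset

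*Protocol article*

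**What the plan says.** All of the definitions stand in the protocol article under Statistics, Data analysis.

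- **Benefit data.** "Data related to intervention benefits will be analysed on the ‘intention-to-treat’ (ITT) principle". The set is then defined as participants analysed by allocated group "regardless of treatment received who complete follow-up data collection and who receive the recommended length of intervention". Scar itch and scar thickness at 6 months are benefit outcomes, so this set governs the primary comparison.
- **Adverse effects.** These are analysed in the same ITT set "as well as per protocol defined as those who received and commenced the intervention".
- **Comparison of the sets.** "A sensitivity analysis will be conducted to compare the ITT and per-protocol approaches if appropriate".
- **Later in the same section.** Multiple imputation of missing dependent and independent data, with ten data sets, is planned as a sensitivity analysis. The section also says that all participants enter the analyses at first, and that the analyses are then repeated by type of surgical intervention.

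Two other sections bear on who would be excluded. Under Discontinuation/adverse events: "Discontinuation or alteration of treatment will be at the discretion of the treating clinical team". The Discussion expects better adherence with the gel than with pressure garments.

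**The concern.** ITT protects the comparison because membership of the set is fixed at randomisation. Here membership depends on two later events: finishing follow-up, and receiving treatment for long enough. The protocol gives reasons why the second may differ by arm. Clinicians who know the allocation may stop or alter treatment, the named adverse effects differ by product, and adherence is expected to differ. If stopping is related to how the scar is doing, the arms are compared among differently selected children, and a difference can appear or vanish for that reason alone.

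The labels do not help a reader recover the randomised comparison. The per-protocol set is defined as "per protocol defined as those who received and commenced the intervention", which asks for less treatment exposure than the set called ITT. Neither set contains every randomised child, so comparing them does not show what the exclusions did.

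**Working it through.** **1. The passages side by side**

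| Set, as labelled | Must have started treatment | Must have completed the recommended length | Must have completed follow-up |
|---|---|---|---|
| ITT | yes, by implication | yes | yes |
| Per protocol | yes | no | not stated |
| All randomised children | no | no | no (no such set is defined) |

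On treatment exposure the ITT set is the narrower of the two, the reverse of normal usage. The ITT definition requires completed follow-up, yet the imputation plan covers missing outcomes. Those two statements do not fit together unless children with incomplete follow-up stay in.

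**2. The plan's own sample size**

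Inputs from Sample size: SD 1.0 mm, difference 0.76 mm, alpha 0.017 per pairwise comparison (two-sided assumed), power 80%, 36 per group, 20% dropout.

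- n per group = 2 × ((2.387 + 0.842) / 0.76)² = 36.1. The stated 36 is reproduced, with normal-approximation power of 79.9%.
- 36 / 0.80 = 45 per group, and 3 × 45 = 135. This is reproduced.
- With the noncentral t, power at 36 per group is 78%. This is the baseline for the next step, so that a change of method is not mistaken for an effect of exclusion.

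**3. Illustration: power if followed children are also excluded for short treatment**

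The share excluded is not in the document. I assume 20% or 40% of the 36.

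| Excluded | n per arm | Power, both arms cut | Power, one arm cut |
|---|---|---|---|
| 0% | 36 | 78% | 78% |
| 20% | 36 × 0.8 = 28.8, taken as 29 | 67% | 72% |
| 40% | 36 × 0.6 = 21.6, taken as 22 | 52% | 64% |

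**4. Illustration: shift with no true effect**

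If a fraction e of one arm is excluded, and those children differ from the retained ones by g mm on average, the mean of the retained children moves by e × g.

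- e = 0.2, g = 0.5 mm: 0.10 mm. Pairwise type I error rises from 0.017 to about 0.026.
- e = 0.4, g = 0.5 mm: 0.20 mm. Type I error is about 0.050.

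A smooth selection model gives a similar range. Let the odds of retention in one arm fall by 0.5 or 1.0 log-odds per mm of thickness, with 60% retention at the mean.

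- Retention is about 59% or 58%, and the mean of the retained children shifts by 0.19 or 0.35 mm.
- 0.19 / 0.76 = 25%, and 0.35 / 0.76 = 46%, of the target difference.
- These figures need a comparator with no selection. If the comparator retains about 75% to 78% with the same slopes, the net shift is only about 0.08 to 0.13 mm.
- If both arms select identically, the net shift is zero.

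**The case against.** The best defence is that the rest of Data analysis shows the intent. It says that all participants are included at first, and it plans imputation of missing outcomes, which makes sense only if non-completers remain. This shows that the section is inconsistent, but it does not repair the definition. The statement about all participants is followed at once by repetition within surgical strata, so it most naturally means pooled before stratified. Imputation is a sensitivity analysis for missing data, and nothing says that it restores children excluded for short treatment, whose outcomes may well have been observed.

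It can also be argued that disregarding treatment received refers to which product was used, with duration as a separate condition. That softens the charge of self-contradiction, but a set conditioned on duration is still not ITT.

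A reader might infer more than the document supports:

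- **That the garment arms could keep nobody.** The Background mentions wear for "up to 18 months or until scar maturation", and follow-up ends at 6 months. But that phrase describes a maximum in general practice. The article does not define the recommended length for the trial period and does not equate it with 18 months.
- **That the cited adherence range shows how many would be lost.** The Discussion reports that "adherence to recommended pressure garment therapy has recently been recorded as 15 to 80" per cent, but in adults, and it concerns adherence. The exclusion turns on length of treatment, and hours of wear are measured separately under Patient adherence.
- **That children who stop for a reaction vanish from the harm results.** They drop out of the ITT harm analysis, but the second analysis, in all who commenced, keeps them.
- **That the 20% allowance covers loss to follow-up only.** Sample size says dropout and does not define it.
- **That exclusions would be hidden.** Patient adherence commits to reporting numbers assigned, treated, completing and analysed.

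**Conclusion.** The point holds on the text alone and needs no calculation. The set governing the primary comparison is conditioned on two post-randomisation events, carries the ITT label, and is narrower on treatment exposure than the set called per protocol. No planned analysis is clearly defined on all randomised children. Allocation is respected, so this is a completer subset analysed by allocated arm, not an as-treated analysis. It selects on duration of treatment, not on daily wear.

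The document does not determine the size. On the assumed exclusions above, power falls from 78% to about 67% or 52%. A null comparison could shift by about 0.1 to 0.35 mm, depending on how far selection differs between the arms, and by nothing if it does not differ. The gel-versus-garment comparisons are the more exposed, because that is where the protocol expects adherence to differ. It should be corrected before analysis, because it fixes the primary analysis population.

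**What to change.** - Delete both conditions from the ITT definition. Define ITT as all randomised children analysed in the allocated arm, including outcomes measured at the scheduled 3- and 6-month reviews after treatment was stopped or changed.
- Apply the planned multiple imputation to this set and say so, so that the definition and the missing-data plan agree. State the main method for children with no 6-month outcome. Make clear that the sentence about including all participants refers to this set.
- Rename the set of children who received and commenced treatment as the treated or safety set, and use it for adverse effects.
- Define the recommended length for the trial period. Use children who completed it only as a supportive per-protocol set.

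The cost is a wording change. The Intervention section says that study follow-up matches standard review times, so no visits are added. The 135 to be recruited does not change: by the noncentral t, power is 78% with 36 children per group measured at 6 months and 88% with all 45. The downside is that the ITT effect may look smaller than the effect in completers.

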##### Patient adherence

*Patient adherence* to wear and care regimes will be defined as ‘the extent to which a person’s behaviour coincides with medical or health advice’ [41]. Adherence will be measured using self-report questionnaires to child and caregiver participants, which will include questions about the number of hours per day of topical silicone gel and pressure garment therapy wear and reasons for nonadherence to interventions. The percentage of patient-reported nonadherence (using the actual hours of wear and recommended hours of wear) will be measured for each intervention group at the 3- and 6-month follow-up [42]. In addition, adherence will be measured and reported by the numbers of patients randomly assigned to each intervention, receiving the intended treatment, time to cessation of the intended intervention, completing the intended intervention as per the protocol, and analysed for the primary outcomes [42].

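### The set labelled per protocol is every child who started treatment, while the set labelled ITT requires completion; comparing them cannot isolate switching, and shows stopping either in reverse or not at all

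*Protocol article*

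**What the plan says.** All the set definitions stand in the Data analysis section of the protocol article.

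- **Benefit outcomes** are analysed by ITT, defined as "participants analysed according to their randomly allocated study group regardless of treatment received" but restricted to those "who complete follow-up data collection and who receive the recommended length of intervention".
- **Adverse effects** get two analyses: "Data related to intervention adverse effects will be analysed according to the ITT principle as well as per protocol". The latter set is "per protocol defined as those who received and commenced the intervention". No other per-protocol definition appears.
- **The comparison** follows at once: "A sensitivity analysis will be conducted to compare the ITT and per-protocol approaches if appropriate". No outcome is named.

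Later in the same section, the analyses are said to begin with all participants before being repeated within surgical strata. Multiple imputation of missing dependent data is planned as a sensitivity analysis.

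Departures from allocated treatment are foreseen. Under Discontinuation/adverse events, "Discontinuation or alteration of treatment will be at the discretion of the treating clinical team". Under Patient adherence, the plan will report time to cessation and the number "completing the intended intervention as per the protocol".

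**The concern.** A reader expects ITT to keep everyone as randomised and per protocol to keep those who followed the allocated treatment. Comparing the two then indicates whether stopping and switching diluted the contrast between arms. Here the per-protocol set has no condition on duration, adherence or staying on the allocated product, while the ITT set does carry a duration condition.

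This matters because the trial is open-label, two of its arms are single products whose combination is the third arm, and the treating team may alter treatment. Movement between arms is plausible. If the two results are set side by side under their present labels, agreement could be taken as robustness to switching when the sets were never able to show it. Disagreement could be interpreted in the wrong direction.

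**Working it through.** **The plan's own numbers.** Inputs from the Sample size section: difference 0.76 mm, SD 1.0 mm, alpha 0.017 (taken as two-sided), power 80%.

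n per group = 2 × (2.387 + 0.842)² × 1.0² / 0.76² = 36.1, which rounds up to 37. The plan states 36, at which power is 79.9%, so the figure is reproduced to within one child. With 20% dropout, 36 / 0.80 = 45 per group and 3 × 45 = 135. No figure in the article depends on the per-protocol definition, so the check that matters is set membership.

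**Who is in which set.**

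| Child | ITT, literal | ITT, all randomised | Per protocol, as defined |
|---|---|---|---|
| Starts, stays on allocated product(s), completes follow-up | in | in | in |
| Starts, stops early, is followed up | out | in | in |
| Starts, switches or adds the other product, treated for the recommended length, followed up | in | in | in |
| Starts, lost to follow-up | out | in | in |
| Never starts | out | in | out |

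**Literal reading.** The sets differ on early stoppers and on children lost to follow-up. Both groups are outside ITT and inside per protocol. If stopping weakens the contrast between arms, the diluted estimate carries the per-protocol label and the completers' estimate carries the ITT label, which is the reverse of what the names promise. A switcher treated for the recommended length is in both sets. If the length condition is taken to mean the allocated product only, the switcher joins the stoppers and the lost children in the difference between sets, and still cannot be separated from them.

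**All-randomised reading.** The sets differ only by never-starters. Stoppers and switchers are in both.

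**How mixed the literal difference would be (illustration only).** Suppose every child starts and the planned 20% dropout occurs.

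- Lost to follow-up: 45 − 36 = 9 per group, in per protocol but not ITT. Overall, ITT is at most 3 × 36 = 108, against 135 commenced.
- The article gives no stopping rate. If 10% to 40% of the 36 followed children stop early, 3.6 to 14.4 more per group leave ITT, so ITT holds about 32 down to 22 per group.
- Stoppers are then 3.6 / (9 + 3.6) = 29% to 14.4 / (9 + 14.4) = 62% of the difference in membership.

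How far the 9 lost children affect a 6-month comparison depends on whether their values are imputed.

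**The case against.** **The definition belongs to adverse effects.** For harms, a commenced-treatment set is a usual choice. This stands. The fault is the label, and its reuse in a comparison with ITT that is not confined to harms.

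**The comparison is conditional and names no outcome.** Also true. That it is meant for the primary outcomes is an inference, but the article gives no other per-protocol set that could serve.

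**Stopping and adherence are handled elsewhere.** Cessation and completion are reported, and adherence, garment pressure and other interventions are listed as time-varying covariates. These are useful, but covariates enter the regressions only if imbalanced between groups, and none of this makes the named comparison do what its label says.

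**The Patient adherence wording is not a rival definition.** Agreed: "completing the intended intervention as per the protocol" is an item in a list of reported counts. It shows only that the data exist.

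**Stronger readings that a reader might infer, and why they fail.**

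- *That the comparison can never show stopping, because the sets differ only by never-starters.* This holds only if ITT is all randomised children. The phrase "participants analysed according to their randomly allocated study group regardless of treatment received" and the imputation of missing outcomes favour that reading. The statement about beginning with all participants does so more weakly, since it may only mean pooling across surgical strata. The written restriction contradicts it.
- *That the number of affected children follows from the Discussion,* where "adherence to recommended pressure garment therapy has recently been recorded as 15 to 80" per cent. That figure concerns adults, and adherence in this trial is measured by hours of wear. Fewer hours is neither stopping nor switching.
- *That the two analyses would share nearly all their children.* This would need a never-start rate, which the article does not give, and it fails on the literal ITT set.
- *That an adverse effect after a switch is counted against the product first started.* The article does not say how events are grouped within the commenced set.

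An article may leave detail to a fuller plan, but here the definitions are stated, and stated in a way that conflicts with their names.

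**Conclusion.** The point holds as a fault in two stated definitions and in the comparison built on them. The per-protocol set is a treated set. The ITT set contradicts itself, since it disregards treatment received and also requires a length of treatment. On the literal text the labels are largely reversed; on the all-randomised reading the comparison is nearly empty of information about departures from treatment. Neither reading isolates switching.

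This conclusion rests on the wording alone and needs no assumed rate. The effect on any estimate cannot be quantified from the article; the set sizes above are illustrative and depend on the assumed 10% to 40% stopping and on every child starting. The definitions should be corrected before analysis. This is not evidence that the trial's comparison of arms is invalid.

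**What to change.** 1. Define ITT as all randomised children analysed by allocated group, with no condition on completing follow-up or on length of treatment.
2. Rename the commenced set as the safety (treated) set and keep it for adverse effects.
3. For a sensitivity analysis of the primary outcomes, define per protocol as children who stayed on their allocated product or products to the 6-month visit and did not receive the trial product not allocated to them.
4. Report that analysis beside the all-randomised result, with the numbers of stoppers and switchers excluded in each arm.

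The inputs are already planned: time to cessation and completion (Patient adherence), number and volume of gel and garment products per participant (Resource use and costs), and other interventions received (Data analysis).

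The cost is revised wording and one tabulation, with no new visits or participants. The per-protocol set so defined will be smaller and open to selection, because children who stay on treatment may differ from those who do not, so its result can only be supportive.
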